#### Sample size calculation

A total number of 640 patients must be completely analyzed. This number is required to simultaneously construct a 97.5%-confidence interval with half-length of 3% for an expected specificity of 90% and a 97.5%-confidence interval with a half-length of 10% for an expected sensitivity of 85% associated with the assumed cut-off and a prevalence of delayed fracture healing of approximately 10%. The 97.5%-confidence intervals are used to maintain a global alpha error of 5%. Assuming a consent rate of 70% among patients meeting all inclusion and exclusion criteria and a dropout rate of 20%, approximately 1,140 patients will need to be screened to enroll 800 participants and obtain 640 complete datasets for analysis. Sample size calculation was done as described by Krummenauer and Kauczor [29]. According to this sample size, we use Harrell's rule that 10 to 20 events per independent predictor variable are necessary to ensure a stable regression model. With the above sample size, approximately 6 predictor variables, respective covariables or confounders 640*0.1/10 can be entered in a final logistic regression model to discriminate regarding the fracture healing outcome [30].

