#### Statistical analyses

An optimal cut-off value for circulating CD8 + TEMRA cell levels (> 38%) was determined in a retrospective pilot study [23]. This predefined threshold, alongside an optimized cut-off identified within the multivariable prediction model, will be used to predict the healing outcome of patients. Based on the final clinical healing classification, sensitivity, specificity and other diagnostic accuracy measures will be calculated for CD8 + TEMRA levels within the covariate-adjusted model. CD8 + TEMRA cells level, together with auxiliary covariates and selected confounders, will be entered into a logistic regression model to predict the occurrence of delayed fracture and non-fracture healing beyond the biomarker alone and/or adjusted. Putative key covariates and confounders are age, sex, diabetes type II, NSAID use, rheumatoid arthritis and osteoporosis. Variable selection will be done using the AIC and validated by using bootstrapping methods. The diagnostic ability of the resulting prediction score will be measured using e.g. Nagelkerkes R2N, Somers Dxy, Brier Score and misclassification error. Further, the score will be analyzed by using AUC/ROC curve and the Youden index. Sensitivity, specificity, NPV, PPV, positive LR and negative LR including 95%-confidence intervals will be calculated. Calibration will be evaluated via calibration plot and goodness-of-fit will be tested using Hosmer–Lemeshow-Test and pseudo-R^2^ measures [30].

For missing data, the proportion of missingness will be assessed. If more than 5% of values are missing, multiple imputation (MI) by chained equations (MICE) will be applied under the assumption that data are Missing Completely at Random (MCAR) or Missing at Random (MAR). The imputation model will include all covariates, outcome variables, and relevant auxiliary variables that may inform the missingness mechanism. A minimum of 20 imputations will be generated. To assess the robustness of the results, sensitivity analyses will be conducted by comparing the multiply imputed datasets with complete-case analyses. Additional variables will be analyzed using appropriate parametric or non-parametric statistical tests, depending on scale and distribution. All p-values from secondary analyses will be interpreted in an exploratory, non-confirmatory manner. All statistical analyses will be done using SAS (version 9.4) and R (latest version at time of analysis).

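### The sample size rests on simultaneous 97.5% intervals for sensitivity and specificity, but the analysis section states only 95% intervals and does not exempt the primary ones

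*Protocol article*

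**What the plan says.** Under Sample size calculation, the protocol article plans to "simultaneously construct a 97.5%-confidence interval with half-length of 3% for an expected specificity of 90" per cent, together with "a 97.5%-confidence interval with a half-length of 10% for an expected sensitivity of 85" per cent. Both refer to the assumed cut-off and to "a prevalence of delayed fracture healing of approximately 10" per cent. The reason for the level is given there: "The 97.5%-confidence intervals are used to maintain a global alpha error of 5" per cent. The resulting requirement is "A total number of 640 patients must be completely analyzed".

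Under Statistical analyses, the accuracy of the biomarker is first mentioned without a confidence level. The text then turns to the logistic model and the prediction score, and after the sentence on the ROC curve and Youden index it says: "Sensitivity, specificity, NPV, PPV, positive LR and negative LR including 95%-confidence intervals will be calculated". No other confidence level appears in that section and no other multiplicity rule is given. The section's exploratory label covers p-values from secondary analyses only.

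**The concern.** The two sections name different confidence levels for measures with the same names. The sample size section splits a 5% error over two intervals, 2.5% each. The analysis section, read literally, gives 5% to each.

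At stake is the property for which the study was sized: one joint statement about sensitivity and specificity, with at least 95% confidence that both intervals cover the true values. An analyst working from the analysis section alone would report intervals too narrow for that statement. If the mismatch stays open until the results are known, the level could also be chosen after the fact.

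**Working it through.** **Inputs** (Sample size calculation): expected sensitivity 0.85, half-width 0.10; expected specificity 0.90, half-width 0.03; prevalence 0.10; level 97.5% for each interval; 640 complete datasets, hence 64 cases and 576 non-cases. From Statistical analyses: level 95%.

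**Step 1: reproduce the plan's figure.** Normal-approximation precision formula, n = z² p(1−p)/d², with two-sided z = 2.2414 for 97.5%.

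- Sensitivity: 2.2414² × 0.85 × 0.15 / 0.10² = 64.05 cases; 64.05 / 0.10 = 640.5 patients.
- Specificity: 2.2414² × 0.90 × 0.10 / 0.03² = 502.4 non-cases; 502.4 / 0.90 = 558.2 patients.

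Sensitivity is the binding requirement and gives the stated 640. The downstream figures follow: 640 / 0.80 = 800 enrolled and 800 / 0.70 = 1,143 screened, stated as about 1,140.

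**Step 2: the same formula at 95%** (z = 1.9600).

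- Sensitivity: 1.9600² × 0.1275 / 0.01 = 48.98, so 49 cases; 49 / 0.10 = 490 patients.
- Specificity: 1.9600² × 0.09 / 0.0009 = 384.1 non-cases; 384.1 / 0.90 = 426.8 patients.

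Planning at 95% would have needed about 490 complete datasets, so about 150 of the 640 (640 − 490) are there to pay for the higher level. The 97.5% is therefore not a slip of the pen.

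**Step 3: half-widths at 64 cases and 576 non-cases.** The standard errors are √(0.1275/64) = 0.04463 and √(0.09/576) = 0.0125.

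| Level | Sensitivity | Specificity |
|---|---|---|
| 97.5% | 2.2414 × 0.04463 = 10.0 points | 2.2414 × 0.0125 = 2.8 points |
| 95% | 1.9600 × 0.04463 = 8.7 points | 1.9600 × 0.0125 = 2.4 points |

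The ratio is 2.2414 / 1.9600 = 1.14, so the planned intervals are about 14% wider.

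**Step 4: simultaneous coverage.** Cases and non-cases are different patients, so at a fixed cut-off the two intervals can be treated as independent.

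- 97.5% each: 0.975² = 95.1%; joint non-coverage 4.94%, at most 2 × 2.5% = 5% without independence.
- 95% each: 0.95² = 90.3%; joint non-coverage 9.75%, at most 2 × 5% = 10% without independence.

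Exact binomial coverage at the planning values points the same way: from 95.4% to 89.9% with Wilson intervals, and from 95.8% to 92.4% with Clopper-Pearson intervals, which are conservative.

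**Step 5: could the level change a reading?** Suppose, for illustration only, that the lower limit for specificity were compared with 90%. With 533 true negatives out of 576 (92.5%), the lower limit is 90.1% at 95% and 89.7% at 97.5%, by Wilson and by Clopper-Pearson alike. The smallest count that clears 90% is 533 against 535 by these two methods, and 532 against 533 by the Wald method. The window is one or two patients.

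**The case against.** **The 95% sentence may concern only the prediction score.** It follows directly on the text about the score, whereas the sample size section ties its 97.5% intervals to the assumed cut-off. Read that way, the two sections are compatible: 97.5% for the two planned intervals, 95% for the score. This reading is possible and cannot be excluded, so it would go too far to say that the multiplicity control has been abandoned. But the analysis section does not draw the distinction, and on this reading it gives no level at all for the primary intervals. The wording needs reconciling either way.

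**A doubled error rate is not a doubled rate of false validation.** A reader might infer from 5% against 10% that the trial becomes twice as likely to validate a marker that falls short. The documents do not support this. The abstract and the aims give targets (at least 30% of impaired healers identified, specificity above 90%, PPV above 60%) without saying that any confidence limit must clear them, and the sample size section plans precision and not a test. If success required both measures to pass, no split of the error would be needed. The protocol does not make that argument and sized the study on the split, so simultaneous coverage is the property to hold it to.

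**The practical effect is small.** This stands. The sample size is unaffected, both levels can be computed from the same counts, and at the planning values no comparison with the stated sensitivity and specificity targets changes: a sensitivity of 85% clears 30% at both levels, and a specificity of 90% does not clear 90% at either.

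**The analysis plan may settle it.** A level merely left open could wait for that document. Here the protocol states two levels, and an analysis plan written from the analysis section would carry 95% forward.

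**Conclusion.** The inconsistency is real and of moderate severity. The study is sized on two simultaneous 97.5% intervals that hold a global 5%, and the analysis section states 95% for measures of the same name without exempting the primary ones. If 95% is applied to them, simultaneous coverage drops from about 95% to about 90%, and the half-widths shrink to the values in the table above.

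The size rests on 64 cases and 576 non-cases, the planning values of 85% and 90%, a fixed cut-off, and independence of the two groups; without independence the bounds on joint error are 5% and 10%. The conclusion is conditional on the literal reading of the 95% sentence, which the text permits but does not force. It concerns coverage only.

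**What to change.** In Statistical analyses, state that sensitivity and specificity at the predefined >38% cut-off will be reported with two-sided 97.5% confidence intervals, as in the sample size calculation, so that the two together hold the global error at 5%. Then state that 95% intervals apply to the prediction score and to PPV, NPV and the likelihood ratios, and that these lie outside the 5% control.

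One consequence should be said openly. The aims name a PPV above 60% as a target characteristic, so it would be misleading simply to call PPV descriptive. The text should note that this aim is not covered by the global error control.

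The cost is one or two sentences. The sample size, data collection and visits do not change. The primary intervals are about 14% wider than at 95%, which is the width for which the 640 patients were planned. The change should be made before healing outcomes are linked to biomarker values, so that the level cannot depend on the results.

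### The Hosmer–Lemeshow test, the only formal fit test named for the prediction score, cannot reveal overfitting if it is run on the one cohort that built the model

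*Protocol article*

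**What the plan says.** The Statistical analyses section of the protocol article enters the TEMRA level and selected covariates into a logistic model. On selection it states: "Variable selection will be done using the AIC and validated by using bootstrapping methods". On fit it states: "Calibration will be evaluated via calibration plot and goodness-of-fit will be tested using Hosmer–Lemeshow-Test and pseudo-R^2^ measures [30". It also lists Nagelkerke's R², Somers' Dxy, the Brier score, misclassification error, AUC/ROC and the Youden index. It names six putative covariates: age, sex, type II diabetes, NSAID use, rheumatoid arthritis and osteoporosis.

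The Sample size calculation section sets the data available: "A total number of 640 patients must be completely analyzed", with "a prevalence of delayed fracture healing of approximately 10" per cent. It limits the model as follows: "With the above sample size, approximately 6 predictor variables, respective covariables or confounders 640*0.1/10 can be entered in a final logistic regression model". No separate validation cohort is described. The section does not say on which data the test is run, sets no threshold for it, and ties no conclusion to its p-value.

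**The concern.** The null hypothesis of the Hosmer–Lemeshow test is that the model fits. Support for the model can therefore come only from failing to reject, and no margin or interval bounds the miscalibration.

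With one cohort, the test falls on the patients used to select and fit the model. The main risk there, with few events per candidate and data-driven selection, is overfitting: predicted risks too extreme for new patients. A same-data test does not address that risk. The bootstrap would address it, but the text attaches it to variable selection and not to calibration.

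At stake is how far the predicted risks can be trusted. The article wants the biomarker to guide treatment before surgery, and a reassuring fit statistic from the fitting data says little about whether the risks hold elsewhere.

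**Working it through.** **1. The plan's own figure.** The inputs are in the Sample size calculation section: "a 97.5%-confidence interval with half-length of 3% for an expected specificity of 90" per cent, "a 97.5%-confidence interval with a half-length of 10% for an expected sensitivity of 85" per cent, and "The 97.5%-confidence intervals are used to maintain a global alpha error of 5" per cent. With n = z²p(1−p)/d² and z = 2.241:

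- Sensitivity: 2.241² × 0.85 × 0.15 / 0.10² = 64.05 cases; 64.05 / 0.10 = 640.5 patients.
- Specificity: 2.241² × 0.90 × 0.10 / 0.03² = 502.4 non-cases; 502.4 / 0.90 = 558.2 patients.

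The larger is about 640, so the plan's figure is reproduced.

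**2. Events per candidate.** 640 × 0.10 = 64 events. The plan's limit is 64/10 = 6.4, about 6 predictors. TEMRA plus the six named covariates makes 7 candidates: 64/7 = 9.1 events each, just below the lower end of the 10 to 20 that the article itself cites.

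**3. Why overfitting cannot show on the fitting data.** A maximum-likelihood logistic fit solves Σ xᵢⱼ(yᵢ − pᵢ) = 0 for every retained column j, including the intercept. The linear predictor LP is a combination of those columns, so Σ(yᵢ − pᵢ) = 0 and Σ LPᵢ(yᵢ − pᵢ) = 0. These are the equations for recalibrating y on LP, and they are met at intercept 0 and slope 1. This holds whether or not the predictors carry information, and after AIC selection too.

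**4. Simulation.** Each dataset has n = 640 and 10% events on average. The article does not give predictor distributions, so these are assumed: TEMRA gamma with mean 27%, age uniform from 18 to 80, and binary covariates with prevalences of 50, 10, 30, 5 and 10%. TEMRA enters as a linear term. The statistic is Σ(O−E)²/[E(1−E/n)] over 10 risk groups, on 8 df, and a pass is p > 0.05. There were 1,500 runs per row, the first 600 also with backward AIC. The last column applies the full seven-predictor model to a new sample of 640.

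| True outcome model | Pass, all 7 predictors | Pass, after AIC | Median slope, new sample |
|---|---|---|---|
| Pure noise | 96.3% | 96.3% | 0.00 |
| Linear, correctly specified | 95.4% | 95.0% | 0.85 |
| Step at 38%, odds ratio 5 | 90.0% | 71.5% | 0.75 |
| Step at 38%, odds ratio 10 | 71.6% | 48.2% | 0.85 |
| Quadratic in TEMRA | 41.9% | 26.0% | 0.82 |
| Omitted TEMRA-by-sex interaction | 36.7% | 33.5% | 0.88 |

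In the noise row, AIC kept at least one predictor in 427 of 600 datasets (71%), and the AIC pass rate refers to those. With 5 to 15 groups and 4,000 runs each, the noise pass rate was 96.4–96.7% (standard error 0.3 points). With 1 to 14 normal predictors it was 95–96%. On a new sample the same test passed the noise models only 52% of the time.

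**5. What the other planned measures would show for noise.** Nagelkerke's R² averaged about 0.02, against about 0.15 for the correctly specified linear model. AUC fell from 0.59 apparent to 0.53 after bootstrap correction. The bootstrap calibration slope averaged 0.44 (60 datasets with 60 resamples each, without repeating AIC).

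**The case against.** A reader might infer that fit is decided by this test and that p > 0.05 will be taken as proof of calibration. The document does not support that. It gives no pass/fail rule, a calibration plot stands beside the test, and p-values from secondary analyses are to be treated as exploratory.

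A reader might also take the 95–97% pass rate for noise as a failure of the test. It is not. A logistic model fitted to noise is correctly specified, so a 5%-level lack-of-fit test should pass it about 95% of the time. The figure shows only that the test answers a different question. Nor does it pass everything: after AIC it let through only about a quarter of the quadratic cases and a third of the interaction cases.

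The other measures give some protection. A bootstrap-corrected AUC or a low R² would expose a worthless score, so endorsement of pure noise is not a realistic outcome. But R², Dxy and AUC do not measure calibration, the Brier score mixes calibration with discrimination, and an uncorrected calibration plot has the same optimism as the test. The milder case remains open: a useful model whose risks are too extreme, like the linear row with slope 0.85.

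Finally, resampling details, the form in which TEMRA enters and the reporting of intervals may sit in an analysis plan that is not shown. Their absence from an article is no fault. What stands is the method that the article does name. Same-data use is an inference, though no other data are described.

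**Conclusion.** The point holds as a minor to moderate one about the prediction score. The only formal fit test named cannot reveal overfitting on the fitting data, which follows algebraically for an unpenalised maximum-likelihood fit. Its power against a wrong functional form is variable: same-data pass rates were about 26–90% in the cases tried, and those figures depend on assumed distributions, forms, effect sizes, 10 groups and linear entry of TEMRA. The article says that the TEMRA level is entered but not that it is linear only, and a classification cut-off of >38% does not mean that the true risk is a step.

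The sample size, the error rate and the primary sensitivity and specificity estimates do not depend on the test. The stronger conclusion, that the trial would certify a useless score, is not supported.

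**What to change.** - Drop the Hosmer–Lemeshow test, or keep it as description with no conclusion attached.
- Report the calibration intercept and slope with confidence intervals, corrected for optimism with the bootstrap already planned, and repeat the full AIC selection in every resample.
- Draw the calibration plot from the bias-corrected curve.
- Check the functional form of TEMRA directly, for example by a likelihood-ratio test of a spline or of an added >38% term.

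The cost is wording and a little more code, with no new data. Reported calibration will look less favourable, because the corrected slope will usually lie below 1. The bootstrap also has limits: for pure noise it gave a slope of 0.44 where the value in new patients was 0.00. It exposes overfitting but can understate it, and should be read with the corrected AUC.

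### The stated robustness check for missing data, imputation under MAR against complete cases, is weak: it can pass while PPV, or sensitivity, is wrong in both analyses

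*Protocol article*

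**What the plan says.** Under Statistical analyses, the article applies chained-equation imputation when more than 5% of values are missing, "under the assumption that data are Missing Completely at Random (MCAR) or Missing at Random (MAR"). The imputation model is to contain covariates, outcomes and auxiliary variables, with at least 20 imputations. Robustness is then addressed in one sentence: "sensitivity analyses will be conducted by comparing the multiply imputed datasets with complete-case analyses". The article states no other missing-data sensitivity analysis.

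Under Sample size calculation, the plan requires complete data: "A total number of 640 patients must be completely analyzed". It assumes "a dropout rate of 20" per cent and concludes that "approximately 1,140 patients will need to be screened to enroll 800 participants and obtain 640 complete datasets for analysis". The other planning inputs are "a prevalence of delayed fracture healing of approximately 10" per cent, a "97.5%-confidence interval with a half-length of 10% for an expected sensitivity of 85" per cent, and an expected specificity of 90% with a half-length of 3 points.

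Aims and Objectives names PPV above 60% and specificity above 90% as target characteristics. The Abstract adds identification of at least 30% of impaired healers.

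**The concern.** A robustness check should be able to fail when the assumption it tests is false. The assumption here is that, given the recorded data, whether the healing outcome is missing does not depend on that outcome. According to Study design, all visits are part of clinical routine, so attendance could plausibly follow healing: a patient who is well may stop coming, and a patient with a problem may be treated elsewhere. The article does not give reasons for dropout, so this is a reasonable worry and not a stated fact.

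Imputation under MAR and complete-case analysis react differently to some such patterns and identically to others. Where they react identically, agreement would be reported as robustness although both estimates are off. The measures at stake are those the study exists to estimate, and sensitivity and PPV rest on few impaired cases. Enrolling 800 protects the number of complete datasets. It does not protect against bias from who leaves.

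**Working it through.** **1. The plan's own figures.** With z = 2.2414 for a 97.5% interval:
- Sensitivity: 2.2414² × 0.85 × 0.15 / 0.10² = 64.05 cases; / 0.10 = 640.5 patients.
- Specificity: 2.2414² × 0.90 × 0.10 / 0.03² = 502.4 non-cases; / 0.90 = 558 patients.
- The larger governs: 640. Then 640 / 0.80 = 800 enrolled, and 800 / 0.70 = 1,143 against the stated 1,140.

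The plan's numbers reproduce. Dropouts: 800 − 640 = 160. Impaired cases among completers: 640 × 0.10 = 64.

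**2. Can the check pass while the answer is wrong?** Take 800 patients with true sensitivity 85%, specificity 90% and incidence 10%. Impaired: 68 test-positive, 12 test-negative. Healed: 72 test-positive, 648 test-negative. True PPV = 68/140 = 48.6%. The dropout patterns below are assumptions. Imputation is represented by filling in healing status from the test result.

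*Pattern A, dropout depends on healing alone (40% of impaired, 17.8% of healed; about 160 lost).*
- Observed: 40.8 and 7.2 impaired; 59.2 and 532.7 healed.
- Complete case: sensitivity 40.8/48 = 85.0%; specificity 532.7/591.8 = 90.0%; PPV 40.8/100.0 = 40.8%.
- Imputation: 40.8% of the 140 test-positives gives 57.1 impaired and 82.9 healed; 7.2/539.9 of the 660 test-negatives gives 8.8 impaired and 651.2 healed. Sensitivity 57.1/65.9 = 86.6%; specificity 651.2/734.1 = 88.7%; PPV 57.1/140 = 40.8%.

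*Pattern B, dropout depends on healing and biomarker jointly (60% of impaired test-negatives, 20% of all others; about 165 lost).*
- Observed: 54.4 and 4.8 impaired; 57.6 and 518.4 healed.
- Complete case: sensitivity 54.4/59.2 = 91.9%.
- Imputation: 54.4/112 of the 140 test-positives gives 68.0 impaired; 4.8/523.2 of the 660 test-negatives gives 6.1. Sensitivity 68.0/74.1 = 91.8%.

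| | Complete case | Imputation | Truth |
|---|---|---|---|
| A: sensitivity | 85.0% | 86.6% | 85.0% |
| A: specificity | 90.0% | 88.7% | 90.0% |
| A: PPV | 40.8% | 40.8% | 48.6% |
| B: sensitivity | 91.9% | 91.8% | 85.0% |

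**3. How far could the unseen outcomes move the results?** Suppose the 640 completers show exactly 85% and 90%: 54.4 true positives, 9.6 false negatives, 57.6 false positives, 518.4 true negatives. Suppose all 160 dropouts lack the outcome but have a biomarker value, with the completers' positivity: (54.4 + 57.6)/640 = 17.5%, or 28 positive and 132 negative.

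At 10% incidence in dropouts (16 impaired, 144 healed):
- All 16 test-negative: sensitivity 54.4/80 = 68%; specificity (518.4 + 116)/720 = 88.1%; PPV 54.4/140 = 38.9%.
- All 16 test-positive: sensitivity 70.4/80 = 88%; specificity (518.4 + 132)/720 = 90.3%; PPV 70.4/140 = 50.3%.

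The incidence in dropouts is not given in the article, so a range is shown:

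| Assumed incidence in dropouts | Unseen cases | Sensitivity | Specificity |
|---|---|---|---|
| 5% | 8 | 54.4/72 = 75.6% to 62.4/72 = 86.7% | 642.4/728 = 88.2% to 650.4/728 = 89.3% |
| 10% | 16 | 68.0% to 88.0% | 88.1% to 90.3% |
| 20% | 32 | 54.4/96 = 56.7% to 82.4/96 = 85.8% | 618.4/704 = 87.8% to 646.4/704 = 91.8% |

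At 20% only 28 of the 32 cases can be test-positive, because only 28 dropouts are.

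**The case against.** The strongest reply is that the two analyses do not rest on one shared assumption. Sensitivity and specificity condition on healing status, so complete-case estimates of them survive dropout that depends on healing alone, as pattern A shows. A reader might infer that agreement says nothing about healing-dependent dropout. That is too strong: under pattern A the two analyses do separate. What remains is that the gap is only 1.6 and 1.3 points, which few would read as a warning, and PPV shows no gap at all. Pattern B needs a link between biomarker and attendance beyond healing. Blinding and a test without influence on care make a direct link less likely, though indirect routes such as age remain.

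A reader might also infer that 160 patients will lack the primary outcome, 2.5 times the 64 cases. The article does not say so. Follow-up runs to week 52 and the primary endpoint is at weeks 17–19, so some dropouts will have the outcome, and others may lack the biomarker instead. The ratio also mixes bases: among 800 enrolled, 80 impaired cases are expected and 160/80 = 2.0. The Abstract speaks of 640 enrolled; the 160 rests on the sample size section.

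Finally, a reader might bound specificity at 72% to 92% by letting all 144 healed dropouts fall on one side of the cut-off. The biomarker is drawn before surgery, so their test results are normally known, and the attainable range is far narrower.

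Two further points are fair. Auxiliary variables and interim visits make MAR more plausible, although the comparison cannot verify it. A full analysis plan, not shown, may add a not-at-random analysis. The point therefore concerns the check that the article does name.

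**Conclusion.** The point holds as a weakness of a stated method, not as an error or contradiction. The named comparison reacts only faintly to dropout driven by healing alone and misses the resulting PPV bias (40.8% against 48.6%). It can miss a sensitivity bias of about 7 points when dropout depends on healing and biomarker together.

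At an assumed 10% incidence in dropouts, the possible downward shift in sensitivity is 17 points (85% to 68%), more than the planned half-length of 10. For specificity it is 1.9 points, inside the planned 3, so specificity is not the main exposure, although even a small shift matters against a target of above 90%.

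These sizes rest on 160 missing outcomes as an upper figure, on known biomarker values with the completers' positivity, and on dropout patterns chosen for illustration. They show what the check could overlook; they do not predict what will happen. With fewer missing primary outcomes the ranges shrink.

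**What to change.** Keep the imputation as planned and keep the complete-case result as a supplement. Add a delta-adjusted (pattern-mixture) imputation, with its settings fixed before unblinding:

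- Vary the odds of impaired healing in patients with a missing outcome, separately above and below the 38% cut-off. The separate variation is what reaches the joint dependence that neither planned analysis handles.
- Report the tipping point at which the article's own targets for sensitivity, specificity and PPV would cease to be met, or would come to be met.
- Give best- and worst-case bounds that use the dropouts' known biomarker values.
- Report how many patients lack the outcome at weeks 17–19 and how many lack the biomarker, so that the upper figure of 160 is replaced by the actual one.

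The cost is a few sentences and extra runs of the same imputation model, with no new patients or data. The downside is that the reported uncertainty may look less favourable.
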